#### Neural mechanism of improvements in cognitive reappraisal inventiveness in individuals cognitively vulnerable to depression through cognitive reappraisal training

Using the group of individuals cognitively vulnerable to depression (divided into intervention and waiting subgroups) and the normal control group as research participants, we will conduct a 4-week (2 sessions/week) CR training program for the intervention subgroup, and before and after training, the intervention and waiting-list control subgroups will undergo fMRI to examine whether CR training can improve reappraisal inventiveness and depression symptoms by regulating the function of the prefrontal–amygdala circuit.

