##### Data analysis

(1) Analysis of the morphological characteristics of brain structure: Voxel-based morphometry (VBM) will be adopted to calculate the concentration and volume of each voxel in different brain tissues (gray matter, white matter, and cerebrospinal fluid) using templates for the whole brain and different brain tissues created based on 3D data, and the volumes of ROIs will be compared between different groups to examine (1) whether the volumes of ROIs before and after CR training differ significantly and (2) if the volumes of ROIs differ significantly, whether the changes in the volumes of the ROIs can predict depressive symptoms immediately after training (T_1_) or 6 months later (T_2_).

(2) Region of interest analysis: The anatomical localization of functional images will be determined with reference to the anatomical maps of the brain in Talairach coordinates and based on the opinions of experienced neuroimagers. Using MARSbar software, the prefrontal subregions (dlPFC/dmPFC/vlPFC/vmPFC) and the amygdala will be extracted as BOLD signals of ROIs by subtraction between the baseline and CR (±) conditions. The data will then be exported to SPSS for statistical processing, in which the activation of the region of interest will be used as a predictor of depressive symptom scores to investigate (1) whether the activation levels of regions of interest (prefrontal lobe and the amygdala and its subregions) before and after CR training differ significantly and (2) if the activation levels do differ significantly, whether the changes in the activation levels of the regions of interest can predict depressive symptoms (T_1_ and T_2_).

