(3) Functional connectivity analysis: Taking the amygdala as the seed point and the average time series within the seed point as the reference time series, we will perform “one point to multipoint” linear correlation analysis with the time series of each ROI. Using the average signals of head movement, the white matter, the cerebrospinal fluid, and the whole brain as covariates and using the prefrontal-amygdala FCs as predictors of depressive symptom scores, we will use between-group *t*-tests, combined with correlation analyses and path analyses, to examine (1) whether the FCs between the prefrontal subregions (dlPFC/vlPFC/dmPFC/vmPFC) and the amygdala before and after CR training differ significantly and (2) if the prefrontal-amygdala FCs do differ significantly, whether the FCs could predict depressive symptoms (T_1_ and T_2_). The FCs between ROIs, cognitive bias (CSQ/NCPBQ), CR ability (RIT), and tendency (ERQ) will then be entered into path analyses to verify the cognitive bias model of CR training.

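### The ROI-activation analysis is stated as before versus after training with no CR-versus-WC contrast, and the volume and connectivity contrasts are left unclear, although the waiting-list arm is scanned twice

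*Protocol article*

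**What the plan says.** The Procedure section on the neural mechanism states that "before and after training, the intervention and waiting-list control subgroups will undergo fMRI". A randomised imaging comparison will therefore exist.

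Under Neuroimaging data, Data analysis, three analyses follow.

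- **Volume (VBM):** "the volumes of ROIs will be compared between different groups to examine (1) whether the volumes of ROIs before and after CR training differ significantly". Then: "if the volumes of ROIs differ significantly, whether the changes in the volumes of the ROIs can predict depressive symptoms" at T1 or T2.
- **ROI activation:** "whether the activation levels of regions of interest (prefrontal lobe and the amygdala and its subregions) before and after CR training differ significantly". Then: "if the activation levels do differ significantly, whether the changes in the activation levels of the regions of interest can predict depressive symptoms" at T1 and T2. No group is named.
- **Amygdala-seed connectivity:** "we will use between-group *t*-tests, combined with correlation analyses and path analyses, to examine" whether prefrontal-amygdala connectivity differs before and after training. Then: "if the prefrontal-amygdala FCs do differ significantly, whether the FCs could predict depressive symptoms".

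A model with time, group and their interaction is written only under Behavioral and self-report data, with CESD as the outcome. The normal controls (NC) are not randomised. They are chosen from the opposite end of the CSQ weakest-link distribution.

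**The concern.** Aim 3 asks how CR training acts on the prefrontal-amygdala circuit. Participants do the CR task in the scanner at T0 and again at T1, so activation may shift through familiarity or habituation with no training at all. A before/after comparison cannot separate that shift from a training effect. A comparison of change between CR and WC can, because both arms share the repeat scan.

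The ROI-activation paragraph states only the first kind of question. For volume and connectivity the groups are mentioned, but a reader cannot tell which of CR, WC and NC are compared, or whether T1 values or T0-T1 changes are. A comparison with NC would not be a randomised one.

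The significance condition adds a second difficulty. A region whose mean does not move may still show individual changes that track symptoms, and the condition drops it. A region that moved only through rescanning may be kept. For connectivity, the step that follows uses the connectivities themselves and not their change.

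**Working it through.** **1. The plan's own figures.** The Normal control group section gives 75 per group, an effect size printed with a doubled decimal point and read here as d = 0.39, 65% power, and 188 after 20% dropout. Assuming a two-sided 5% level (the article states none):

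- Noncentral t, noncentrality 0.39 × √(75/2) = 2.39, df 148: power 66.0% (normal approximation 66.6%).
- 150 / 0.8 = 187.5, rounded up to 188.

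Both reproduce. They concern the depression score; no imaging power is stated.

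**2. The three analyses side by side.**

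| Analysis | Groups named? | Question asked | Conditional on significance? | Carried to symptom step |
|---|---|---|---|---|
| Volume | Yes, not which | Before/after | Yes | Change in volume |
| ROI activation | No | Before/after | Yes | Change in activation |
| Connectivity | Between-group t-tests, not which groups | Before/after | Yes | Connectivity, not its change |

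None of the three states a CR-versus-WC difference in change.

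**3. Illustration of the before/after test.** Assumptions, none of them in the article: no training effect; a repeat-scan shift common to both arms, dz, in units of the SD of within-person change; two-sided 5%. The n of 75 is borrowed from the clinical calculation, and 30 is shown as a lower case. The CR-only paired t-test has noncentrality dz × √n and n − 1 df, for example 0.2 × √75 = 1.73 and 0.4 × √75 = 3.46.

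| dz | CR-only rejects, n = 75 | CR-only rejects, n = 30 |
|---|---|---|
| 0 | 5.0% | 5.0% |
| 0.1 | 13.7% | 8.3% |
| 0.2 | 40.1% | 18.5% |
| 0.3 | 72.7% | 35.5% |
| 0.4 | 92.8% | 56.3% |

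**4. The randomised comparison.** The expected difference in change is dz − dz = 0, so the shared shift cancels. In 20,000 simulated trials with 75 per arm, at dz = 0, 0.1, 0.2, 0.3 and 0.5, the CR-versus-WC t-test of change rejected in 4.8% to 5.2%.

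**5. Multiplicity, a separate matter.** Five ROIs each tested at 5% give 1 − 0.95^5 = 22.6% chance of at least one false positive. A count of 19 tests (5 volumes, 5 ROIs × 2 activation contrasts, 4 amygdala connections) gives 1 − 0.95^19 = 62.3%. Both assume independence and no correction. They would be the same for CR-versus-WC tests, so they bear on error control and not on the missing contrast.

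**The case against.** The strongest reply is that the before/after phrase may be only a time label for T0 and T1. WC is also scanned at both times, the trial has a stated group-by-time design, and the article never says the ROI test is a paired test within CR. A condensed article may leave model terms to a fuller document. This stands in part: the text does not prove that a CR-only paired test is intended. But the design is set out under the behavioral heading, the interaction is written for CESD alone, and the ROI paragraph does state its question, without the comparison that aim 3 needs.

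Four stronger readings are tempting and should not be made.

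- *That all the imaging analyses lack a group comparison.* The volume paragraph compares groups and the connectivity paragraph uses between-group t-tests. The fault there is an unclear contrast.
- *That the connectivity t-tests are at a single time point.* The text does not say so; a t-test of change between groups is an equally natural reading.
- *That the rejection rates above are properties of this plan.* They rest on an assumed shift, level and sample size. Some scans will be excluded for motion or artefact. Activation is also a subtraction between CR and baseline viewing, so habituation common to both conditions cancels and only a shift specific to that contrast matters.
- *That the significance condition biases the symptom slopes.* Selecting on a large mean change inflates the reported mean change, but does not in itself distort the relation between individual change and CESD. The later path analyses also enter connectivities without repeating the condition.

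The Discussion calls its expectations about post-training change exploratory. That lowers the weight of the point but does not remove it, because attributing change to training still needs the control arm.

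**Conclusion.** The point holds in a limited form. The ROI-activation analysis, as stated, omits the randomised contrast that the design makes available. For volume and connectivity, the comparison groups and the quantity compared need to be named. In all three, the first symptom-prediction step depends on a prior significant result. The documents do not support the wider inference that aim 3 as a whole rests on an uncontrolled comparison.

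The direction of the risk is clear, but its size cannot be fixed from the article. For an assumed shift of 0.2 to 0.4 SD of change, a CR-only test would be falsely positive in about 40% to 93% of trials with 75 scans, or 19% to 56% with 30, against about 5% for CR versus WC. With no shift specific to the activation contrast, the excess disappears. The mechanistic aim is affected; the CESD primary outcome is not.

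**What to change.** - For every prespecified ROI volume, activation contrast and amygdala connection, define the training-effect test as the CR-minus-WC difference at T1 adjusted for the T0 value. Keep NC as a descriptive reference.
- Apply Holm or false-discovery-rate control within each of the three families.
- Run the symptom-prediction models for all prespecified ROIs whatever the first-step p-value, using change in the measure (for connectivity too) and adjusting for arm and T0 CESD.

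The cost is analysis wording only: the same scans and ROI extracts serve. Power is somewhat lower than for a paired pre-post test. With equal SD of change in both arms, the standard error of a difference in change is √2 ≈ 1.41 times that of the single-arm mean change, before any gain from T0 adjustment. The Ethics statement says nobody had been recruited at submission, so on the article's account the change could be made before any data were seen.

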### Statistical analysis

#### Behavioral and self-report data

##### Intervention effect analysis

A 3 (group: CR = cognitively vulnerable intervention subgroup; WC = cognitively vulnerable waiting-list control subgroup; NC = normal control group) × 3 (time point: T_0_ = pretraining, T_1_ = post-training, T_2_ = 6-month follow-up) mixed design will be adopted. Using the HLM analysis, as well as mediating/modulating effect analyses, we will investigate (1) hypothesis 1, whether the changes in negative cognitive biases and depressive symptoms across time 1 and time 2 differ significantly among groups and (2) hypothesis 2, whether the changes in negative cognitive bias (negative interpretation bias and/or negative rumination bias) pre- and post-training could predict depression symptoms at T_1_ and/or T_2_.

To test hypothesis 1, we will conduct an HLM analysis with time (0 = pretraining; 1 = post-training), group (0 = CR; 1 = WC; 2 = NC), and the interaction between time and group as predictor variables and the with CESD score as the outcome variable. To test hypothesis 2, we will conduct mediating/modulating effect analyses among CR ability (RIT) and tendency (ERQ), negative cognitive bias (NCPBQ), cognitive vulnerability (CSQ), and depressive symptoms (CESD) at T_1_ and/or T_2_. The HLM and mediating/modulating effect analyses will be conducted in SPSS (Statistical Product and Service Solutions) software version 22.0 (SPSS, Inc., Chicago, IL, United States) combined with the PROCESS Macro (Hayes, 2012).

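### The region-of-interest activation analysis names no comparison with the waiting-list arm, so change shared by both arms on repeat scanning could be read as a training effect

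*Protocol article*

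**What the plan says.** All references are to the protocol article.

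- **Activation.** Under Neuroimaging data, Data analysis, item (2), the first question is "whether the activation levels of regions of interest (prefrontal lobe and the amygdala and its subregions) before and after CR training differ significantly". The second is conditional on the first: "if the activation levels do differ significantly, whether the changes in the activation levels of the regions of interest can predict depressive symptoms". The only modelling role given is that "the activation of the region of interest will be used as a predictor of depressive symptom scores".
- **Volumes.** Item (1) of the same section says that "the volumes of ROIs will be compared between different groups to examine".
- **Connectivity.** Item (3) says "we will use between-group *t*-tests, combined with correlation analyses and path analyses".
- **Who is scanned.** The Procedure subsection on the neural mechanism says that "before and after training, the intervention and waiting-list control subgroups will undergo fMRI".
- **Symptoms.** The hierarchical linear model under Intervention effect analysis includes time, group "and the interaction between time and group as predictor variables". It sits under Behavioral and self-report data, and its stated outcome is the CESD score.
- **Aim.** The opening paragraph of Methods also words the activation aim as a change from before to shortly after training, without a comparator.

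**The concern.** A change in prefrontal and amygdala activity is a central link in the mechanism that the trial sets out to test. Participants do the reappraisal task in the scanner at T0 and again at T1. On the second occasion those in both arms have met the task and the scanner before, so activation may shift without any training. Only a comparison of change between the randomised arms separates that shift from an effect of training.

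Item (2) states no such comparison. Its named model has activation on the predictor side and symptoms as the outcome, so it does not answer the item's own first question. The result also carries forward: a significant change in activation is the condition for going on to symptom prediction, so an uncontrolled test in the first step could trigger the second.

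**Working it through.** **1. The three imaging items side by side**

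| Item | Question posed as pre/post training | Group comparison named |
|---|---|---|
| (1) Volumes | yes | yes, between groups |
| (2) Activation | yes | none |
| (3) Connectivity | yes | yes, between-group t-tests |

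The group-by-time model for CESD does not fill the gap, because it is specified for symptom data.

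**2. The protocol's own figure**

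The sample size section gives 75 per group, 65% power and an effect size printed with a misplaced decimal, read here as d = 0.39. Alpha is not stated; two-sided 0.05 is assumed.

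- Normal approximation: power = Φ(d√(n/2) − 1.96) = Φ(0.39 × √37.5 − 1.96) = Φ(2.388 − 1.96) = 66.6%. The exact t calculation gives 66.0%.
- Dropout: 150 / (1 − 0.20) = 187.5, rounded up to 188.

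The stated figures reproduce. They concern symptom scores; no sample size is given for imaging. The value 75 is borrowed below only as a plausible arm size.

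**3. Illustration of what the missing contrast could cost**

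Assumptions: the true training effect is zero, and both arms have the same mean shift δ from T0 to T1, in SDs of the within-person change score. The test is two-sided at 0.05. The values of δ are assumed; the protocol gives none.

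*Pre-post test in the CR arm only.* The paired t statistic has n − 1 degrees of freedom and non-centrality δ√n. The rejection probability is P(|T| > t(0.975, n − 1)). For n = 75 the critical value is 1.9925.

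| δ | δ√75 | Rejects, n = 75 | Rejects, n = 60 | Rejects, n = 94 |
|---|---|---|---|---|
| 0 | 0 | 5% | 5% | 5% |
| 0.1 | 0.866 | 14% | 12% | 16% |
| 0.2 | 1.732 | 40% | 33% | 48% |
| 0.3 | 2.598 | 73% | 63% | 82% |

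Here 60 is 75 less 20%, to allow for scans lost to motion or other causes, and 94 is 188 / 2. All figures are per region.

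*CR versus WC on the change score.* The expected difference is δ − δ = 0 for every δ, so the test keeps its nominal level. A simulation with 20,000 runs and 75 per arm gave 4.8% to 5.2% for δ from 0 to 0.5.

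**The case against.** The strongest reply is that the pre/post wording is only a time label. The volume and connectivity items use the same wording and still name group comparisons, and the Procedure section applies similar wording to both vulnerable subgroups. This stands. A reader might infer that the protocol prescribes a paired test in the trained arm and throws away its randomised comparison. The documents do not support that: no paired test is named, the sample is not limited to the CR arm, and scanning the waiting-list arm twice suggests that it was meant as a comparator.

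A second reply is that a condensed article may leave the contrast to a fuller plan. That would carry more weight if the article were silent on all three imaging analyses. It names a group comparison for two and, for the third, states a question and a model that do not match. This is a poorly stated analysis rather than omitted detail.

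Third, the activation measure subtracts the viewing baseline from the reappraisal conditions, so a session-wide shift common to both would largely cancel. This also stands, and it argues for caution about the size of the drift. It does not remove practice specific to the reappraisal condition.

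Finally, the Discussion describes the hypothesis on post-training changes as exploratory, and the primary outcome is CESD. That lowers the severity but does not make an uncontrolled change attributable to training.

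**Conclusion.** The point holds for the activation analysis only. As written, item (2) gives a question and a model that together provide no randomised contrast, whereas its two neighbours name one. Any non-zero drift shared by the arms inflates a one-arm pre-post test and cancels in CR versus WC, so the direction of the problem does not depend on the assumed figures.

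The size does depend on them. The rejection rates of 14%, 40% and 73% rest on assumed drifts of 0.1, 0.2 and 0.3 SD, on 75 analysable scans per arm, and on a CR-only paired test that the protocol does not name. They show what could follow from a literal reading, not what will be reported.

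Severity is moderate. The finding bears on the mechanistic claim and on the symptom-prediction step that hangs on it. It does not touch the primary CESD comparison, which has a group-by-time term, and it should not be extended to the volume or connectivity analyses.

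**What to change.** In Data analysis, item (2):

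1. State the first question as the CR-versus-WC difference in T0-to-T1 activation for each region of interest. Use either T1 activation adjusted for T0 or an arm-by-time term in the two randomised arms; choose one in advance.
2. Describe within-arm change as descriptive only.
3. Make the second question depend on the between-arm contrast, not on a pre-post difference.
4. Place the model in which activation predicts symptom scores under the second question only.

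The cost is a few sentences. Both arms are already due to be scanned twice, so no new data are needed, and the Ethics statement says that nobody had been recruited at submission.

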On the other hand, the frequent user of CR showed stronger downregulation of amygdala activation to negative emotion stimuli (Kanske et al., 2012), and CR in healthy individuals can attenuate the excitatory connectivity from the dlPFC to the inferior frontal gyrus (IFG) and increase the inhibitory connectivity from the IFG to the dlPFC, which supports the selection of appropriate alternative CR strategies (reinterpretations) in the IFG, and afterward, inhibition of original interpretations maintained and monitored in the dlPFC (Morawetz et al., 2016). Neurofeedback-guided CR training targeting the left vlPFC improved the frequency of CR strategy use (indexed with ERQ) as well as depression symptoms (Keller et al., 2021). Therefore, CR training may enhance CR ability by changing the functional activity/connectivity pattern of prefrontal-amygdala circuits, which then alleviates cognitive biases and thus depressive symptoms.

Researchers suggested that specific measures using lab-based tasks may be more sensitive to detect training effects (Cohen and Ochsner, 2018). Therefore, in this study, we will combine the RIT, CR training, and fMRI, as well as self-report measures (cognitive/emotion/symptoms) to address the following aims: (1) to examine whether the CR ability (reappraisal inventiveness) of the population with cognitive vulnerability to depression is abnormal; (2) to test the hypothesis that CR training alleviates depressive symptoms through the mediators of cognitive bias (e.g., interpretation bias and/or rumination bias); (3) to investigate the neural substrates (structural/functional) of prefrontal–amygdala circuits through which CR training improves the ability to generate a CR strategy; and (4) to examine the short- and/or long-term effects of CR training on reducing depression symptoms in cognitively vulnerable individuals immediately after intervention and/or 6 months to provide theoretical and practical evidence for early intervention in these populations. We postulate that CR training improves CR ability (RIT) by changing the brain activity/function connectivity of the prefrontal-amygdala circuits, thereby reducing negative cognitive biases (NCPBQ-NIB, NCPBQ-NRB, and CSQ) and improving depression symptoms (CESD) (Figure 1).

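### The neural predictor of depressive symptoms is a pre-post change for volume and activation but simply the FC, with no change term or time point, for connectivity

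*Protocol article*

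**What the plan says.** The data analysis part of the neuroimaging section (Protocol article, Statistical analysis) uses one two-step template for three neural measures. Step one asks whether the measure differs before and after training. Step two, taken only if it does, asks whether it predicts depressive symptoms at T1 and/or T2. The step-two predictor is:

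- Item (1), volume: "whether the changes in the volumes of the ROIs can predict depressive symptoms immediately after training".
- Item (2), activation: "whether the changes in the activation levels of the regions of interest can predict depressive symptoms".
- Item (3), connectivity: "if the prefrontal-amygdala FCs do differ significantly, whether the FCs could predict depressive symptoms (T_1_ and T_2".

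The lead-in to item (3) also names the FCs themselves ("using the prefrontal-amygdala FCs as predictors of depressive symptom scores"). The FCs, with the cognitive bias and reappraisal measures, "will then be entered into path analyses to verify the cognitive bias model of CR training". The Introduction states the hypothesis to be tested: "CR training improves CR ability (RIT) by changing the brain activity/function connectivity of the prefrontal-amygdala circuits". The opening of the Methods lists changes in activation and connectivity among the things to be explored, and the Discussion asks whether training will change prefrontal-amygdala FCs.

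**The concern.** One question, whether the neural effect of training relates to later symptoms, is put in terms of change for two measures and not for the third. Connectivity is also the neural measure that the article names for the path analysis.

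An FC value from a single scan mixes whatever training altered with stable differences between people. If those stable differences are related to depressive symptoms, an FC level will correlate with a CESD level even when no one's change in FC has anything to do with their symptoms. Neither the imaging items nor the path analysis states an adjustment for T0 CESD. A significant result could then be taken as support for the mechanism when it shows only a standing association, and it could not be set beside the volume and activation results, which answer a different question.

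**Working it through.** **1. Comparing the wording.** The template, the condition and the outcome are the same in all three items; only the predictor differs.

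| Measure | Predictor in the numbered question | Time reference of predictor |
|---|---|---|
| ROI volume | change | before to after training |
| ROI activation | change | before to after training |
| Prefrontal-amygdala FC | the FC | none |

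The lead-in to the activation item is also loose ("in which the activation of the region of interest will be used as a predictor of depressive symptom scores"), but its numbered question then specifies change. The contrast therefore rests on the numbered questions, not on the lead-ins.

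**2. What a level-on-level test picks up.** The document gives no figure to reproduce here, so this is an illustration.

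From the document: n = 75 per group (sample size paragraph under Normal control group).

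Assumed, not in the document: two-sided 0.05; observed correlation r between FC level and CESD level of 0.15 to 0.30, arising wholly from stable traits; FC retest correlation 0.5; CESD stability 0.6; no link between FC change and symptoms.

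The share of significant level-based tests is then the power of a Pearson test at r. By Fisher's z, the expected statistic is atanh(r) × √(n − 3), with √72 = 8.485:

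| r | atanh(r) | expected z | share significant | simulated (3,000 runs) |
|---|---|---|---|---|
| 0.15 | 0.1511 | 1.28 | 25% | 24% |
| 0.20 | 0.2027 | 1.72 | 41% | 40% |
| 0.25 | 0.2554 | 2.17 | 58% | 59% |
| 0.30 | 0.3095 | 2.63 | 75% | 75% |

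With the change T1 minus T0, the stable part cancels and the simulated share is about 5% throughout.

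A second simulation set the correlation between latent traits at 0.3 to 0.5, FC reliability at 0.4 to 0.7 and CESD stability at 0.6. The implied observed correlations run from 0.3 × √(0.4 × 0.6) = 0.15 to 0.5 × √(0.7 × 0.6) = 0.32. At n = 75 the T1 FC level was significant in 25% to 83% of runs, and the change in about 5%.

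**3. Does the pre-post condition protect?** In that second simulation everyone's FC moved by 0.5 SD (assumed), unrelated to symptoms. A paired pre-post test passed in 97% to 100% of runs at n = 75. A uniform shift satisfies the condition and leaves the trait correlation untouched.

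**4. Where the problem sits.** FC level against symptom change (T1 minus T0 CESD) was significant in only about 4% to 5% of runs. The fault is the pairing of a level with a level, so the missing baseline CESD term matters as well as the FC wording.

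**5. A tempting remedy that falls short.** Entering T1 FC together with T0 FC looks equivalent to using the change. With r = 0.30 at both times and retest 0.5, the partial correlation of T1 FC with CESD is (0.30 − 0.30 × 0.5) / √[(1 − 0.09)(1 − 0.25)] = 0.15 / 0.826 = 0.18. At n = 150 the expected z is atanh(0.18) × √146 = 2.2, or about 60% significant. Adding T0 CESD brought the simulated share down to about 8% to 22% across r = 0.15 to 0.30, still above 5%. A noisy T0 FC removes only part of the trait.

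**The case against.** The strongest reply is that the connectivity phrase is shorthand. Its second question depends on its first, the before-and-after comparison, so the FCs may mean the FC changes. The Introduction, Methods and Discussion all speak of changed connectivity, and an article condenses a fuller protocol. This stands in part. A reader might infer that the plan has settled on FC levels; the text does not establish that. It leaves the predictor undefined where the two parallel items define it, and what it literally names is a level.

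A reader might also infer that the plan will report connectivity as predicting the benefit of training. The wording is depressive symptoms, not benefit. The step to a training mechanism comes only from the later use of FCs in the path analysis, whose structure is not given.

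The percentages are open to the charge of circularity: they are the power of a correlation test at correlations that were assumed. That is correct. They show what would follow if a stable association of that size exists; they are not evidence that it does.

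Finally, the stakes are limited. The Discussion calls the hypothesis about changes after training exploratory and claims only proof of concept for the model, and the randomised comparison of CESD by HLM is separate.

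What survives is narrower but real. This is more than omitted detail: the article does specify the predictor for each measure, and it does so inconsistently in adjacent items.

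**Conclusion.** The point holds as an inconsistency in a secondary, mechanistic analysis that should be corrected. Read as written, the connectivity test cannot distinguish a stable FC-symptom association from an effect of changed connectivity, and the significance condition before it does not help.

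The size is conditional: about 24% to 75% misleading positives per FC at n = 75 if the stable correlation is 0.15 to 0.30, against about 5% for the change score. The 5% assumes that the stable component contributes equally to FC at T0 and T1. If FC changes were meant all along, the remedy is only a clarification. Nothing here touches the primary CESD comparison.

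**What to change.** In item (3), replace the second question with: *whether the changes in the FCs (T1 minus T0) can predict depressive symptoms at T1 and T2, with T0 CESD as a covariate*. Use the same FC change term in the path analysis. State the T0 CESD covariate for volume and activation too, since their outcome is also a T1 or T2 symptom level. Do not substitute a model with T1 FC adjusted for T0 FC, for the reason shown in the working.

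The cost is one sentence and no new data: fMRI before and after training is already planned in the intervention and waiting-list subgroups, and the ethics statement says no participant had been recruited at submission. The downside is that change scores are noisier than levels, so the FC result will be significant less often.
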